## Abstract

**Background:**

Non-suicidal self-injury (NSSI) has become a substantial public health problem. NSSI is a high-risk marker for the development and persistence of mental health problems, shows high rates of morbidity and mortality, and causes substantial health care costs. Thus, there is an urgent need for action to develop universal prevention programs for NSSI before adolescents begin to show this dangerous behavior. Currently, however, universal prevention programs are lacking.

**Methods:**

The main objective of the present study is to evaluate a newly developed universal prevention program (“DUDE – Du und deine Emotionen / You and your emotions”), based on a skills-based approach in schools, in 3200 young adolescents (age 11–14 years). The effectiveness of DUDE will be investigated in a cluster-randomized controlled trial (RCT) in schools (*N* = 16). All groups will receive a minimal intervention called “Stress-free through the school day” as a mental health literacy program to prevent burnout in school. The treatment group (*N* = 1600; 8 schools) will additionally undergo the universal prevention program DUDE and will be divided into treatment group 1 (DUDE conducted by trained clinical psychologists; *N* = 800; 4 schools) and treatment group 2 (DUDE conducted by trained teachers; *N* = 800; 4 schools). The active control group (*N* = 1600; 8 schools) will only receive the mental health literacy prevention. Besides baseline assessment (T0), measurements will occur at the end of the treatment (T1) and at 6- (T2) and 12-month (T3) follow-up evaluations. The main outcome is the occurrence of NSSI within the last 6 months assessed by a short version of the Deliberate Self-Harm Inventory (DSHI-9) at the 1-year follow-up (primary endpoint; T3). Secondary outcomes are emotion regulation, suicidality, health-related quality of life, self-esteem, and comorbid psychopathology and willingness to change.

**Discussion:**

DUDE is tailored to diminish the incidence of NSSI and to prevent its possible long-term consequences (e.g., suicidality) in adolescents. It is easy to access in the school environment. Furthermore, DUDE is a comprehensive approach to improve mental health via improved emotion regulation.

**Trial registration:**

German Clinical Trials Register (DRKS) DRKS00018945. Registered on 01 April 2020, https://www.drks.de/drks_web/navigate.do?navigationId=trial.HTML&TRIAL_ID=DRKS00018945

## Background

### Non-suicidal self-injury

Non-suicidal self-injury (NSSI) has gained increasing importance in recent years, from both a clinical and socio-political perspective. According to the World Health Organization (WHO), self-injurious behavior represents the fifth most frequent health risk in adolescence [1], and it affects approximately 17–18% of adolescents worldwide [2]. NSSI is characterized by the intentional and self-inflicted destruction of body tissue without suicidal intent [3]. Above all, it is a high-risk marker for the development and persistence of mental health problems in adolescents, and has been highlighted by researchers all over the world. NSSI is a predictor of suicidal behavior [4, 5]; it is strongly associated with comorbid psychopathology (e.g., depression, anxiety disorders, posttraumatic stress disorder, borderline personality disorder) [6, 7] and other high-risk behaviors (e.g., substance abuse, suicidal thoughts) [8, 9]. Furthermore, NSSI causes substantial costs for the health system [10]. Given that NSSI is a common and highly recurrent behavior that peaks in adolescence around the age of 16 years [11, 12], there is an urgent need for action, especially in the area of universal prevention, prior to the age of 11 to 14 years when adolescents begin to show these dangerous behaviors.

### Universal prevention programs targeting NSSI

So far, universal prevention programs are lacking. Targeted prevention programs (*n* = 21) currently outnumber universal approaches (*n* = 2) and focus on adolescents with a history or current episodes of NSSI and mostly comorbid mental health problems [13].

Targeted approaches have been found to significantly reduce NSSI and improve mental health [14, 15]. However, access to these treatments is limited due to a lack of resources (e.g., effective interventions for adolescents addressing NSSI are not available across all regions) and an insufficient number of specially trained clinicians [16]. To the best of our knowledge, only two school-based universal prevention programs for adolescents are available to date [17, 18]. The signs of self-injury (SOSI) program by Muehlenkamp and colleagues [18] attempts to increase knowledge, improve help-seeking attitudes and behaviors, and decrease NSSI through the use of psychoeducational elements within one module for students and one module for faculty/staff. An uncontrolled pre-post evaluation of 274 adolescents (mean age 16.07) indicated that the prevention program increased knowledge, improved help-seeking attitudes and help-seeking intentions among the students, and did not produce iatrogenic effects. However, there were no significant changes with regard to help-seeking actions [18]. A study by Baetens et al. [17] examined differences between the programs Happyles and HappylesPLUS targeting NSSI in 651 Belgian school pupils (mean age = 12.85 years) using a randomized pre-post design. Happyles is a stepped-care prevention program which focuses on enhancing general mental well-being and social connectedness. It is based on an eclectic approach, which is grounded in positive psychology, cognitive-behavioral therapy, and problem-solving [19]. While Happyles consists of a general in-classroom education program, HappylesPLUS additionally incorporates an in-classroom one-hour psychoeducation module on NSSI. As with the aforementioned SOSI program, no iatrogenic effects were found. However, no significant difference emerged between the two groups regarding the incidences of engagement in NSSI, although pupils did report a reduced likelihood of possible engagement in future NSSI, and an increased emotional awareness was observed [17].

Consequently, there is not yet any universal prevention program which has been found to reduce NSSI. SOSI is similar to gatekeeper training for suicide prevention, and HappylesPLUS tries to reduce NSSI through 1 h of psychoeducation on the basis of a program that was not originally developed to address NSSI, even though studies in the field of universal prevention of suicidality show the best evidence for skills-based approaches [13, 20]. For example, the SEYLE study (Saving and Empowering Young Lives in Europe) compared the three most frequently employed types of suicide prevention (early detection/screening by professionals, gatekeeper training, skills-based group training) in a four-arm randomized controlled trial over a period of 12 months with 11,110 adolescents (mean age 15 years). According to the mentioned systematic reviews, only the interactive skills approach of a school-based universal prevention program YAM (Youth Aware of Mental Health) was associated with a significant reduction in severe suicidal ideation and incident suicide attempts compared with the control group [21]. As NSSI has been found to be a predictor of suicidality, the implication may be derived that the key to effective prevention lies in skills-based group training.

### Reason for the trial

NSSI has become not only a clinical but also a huge public health problem. Above all, it represents a high-risk marker for the development and persistence of mental health problems including high rates of morbidity and mortality, and causes substantial costs for the health system. While there are targeted prevention programs which have been shown to be effective, to date, only two school-based universal prevention programs exist (SOSI and HappylesPLUS), and these were found not to reduce NSSI. Thus, there is a gap between the necessity for universal prevention of this epidemic problem and the availability of such programs. As it has been proven that skills-based approaches in targeted prevention might change the tragic development of suicidality [14], increased efforts should be undertaken to develop universal prevention programs based on a skills-based approach in order to reduce NSSI in a school setting.

### Objectives and aims

The main objective of the present study is to evaluate a newly developed universal prevention program (“DUDE – Du und deine Emotionen / You and your emotions”) based on a skills-based approach in schools, in 3200 young adolescents (age 11–14 years). The effectiveness of DUDE will be tested in a cluster-randomized controlled trial (RCT), meaning that the participating schools (*N* = 16) will be randomly assigned to the respective conditions (see the “Procedure and randomization” section). All groups will receive a minimal intervention with a booklet called “Stress-free through the school day” as a mental health literacy prevention against burnout in school. The treatment group (*N* = 1600; 8 schools) will be divided into: treatment group 1 (DUDE will be conducted by trained clinical psychologists; *N* = 800; 4 schools) and treatment group 2 (DUDE will be conducted by trained teachers; *N* = 800; 4 schools). The active control group (*N* = 1,600; 8 schools) will only receive the mental health literacy prevention. The main outcome is the occurrence of NSSI within the last 6 months assessed by a short version of the Deliberate Self-Harm Inventory (DSHI-9) at the 1-year follow-up (primary endpoint; T3). We hypothesize that DUDE will show a lower incidence of NSSI compared to the active control group, demonstrating its superiority. In addition, secondary outcomes such as emotion regulation and suicidality, health-related quality of life, self-esteem as well as comorbid psychopathology, and willingness to change will demonstrate the superiority of DUDE over the active control group.

### Primary hypothesis

Participants in the treatment group (1 or 2) receiving DUDE will show a lower occurrence of NSSI within the past 6 months at T3 compared to students in the active control group.

## Methods/design

### Setting and recruitment

The present trial is a study from the newly founded German Centre of Prevention Research in Mental Health at the University of Wuerzburg in Germany. The aim of this center is to develop and implement existing prevention programs, evaluate their efficacy and effectiveness, and ensure their sustainability and broad dissemination.

In the present trial, we aim to include *N* = 3200 young adolescents (age 11–14 years) in Germany within a school-based setting with 16 schools. There are several reasons why the school setting is ideally suited for this trial: (1) First of all, NSSI is a phenomenon with epidemic proportions. Based on the high prevalence and the possible outcomes of NSSI, a school-based setting and population is reasonable in terms of universal prevention. (2) As mentioned, there is a need to further develop and evaluate universal prevention in the field of NSSI (see the “Background” section). (3) Targeted trials entail a selection bias, meaning that access is often limited to the location where the targeted prevention is implemented (mostly universities or clinics). Furthermore, adolescents will not be stigmatized during the allocation process. Hence, even if adolescents are suffering and undergoing emotional struggles but are afraid or reluctant to ask for help, they will eventually benefit from the participation in DUDE. Therefore, their risk of developing mental health problems in general, and engagement in NSSI in particular, might be decreased.

The recruitment of the 16 schools will occur in collaboration with the Bavarian Ministry of Education and Cultural Affairs. First, the schools will be selected at random by a staff member of the Ministry. Following this, the schools will be randomly assigned (cluster randomization) to the treatment group (1 or 2) or to the active control group using cluster randomization by an assigned external researcher who is not part of the study group. All eligible pupils of the participating schools will be offered the chance to participate in the study. The assessment time points of the study are before the start of treatment (baseline, T0), at the end of the treatment (T1), 6 months after the end of treatment (T2), and 12 months after the end of treatment (T3) in order to evaluate the efficacy of the universal prevention. The flow chart of the trial is shown in Fig. 1 and the trial schedule is depicted in Fig. 2.

**Fig. 1 Fig1:**
[figure not shown]
Study flow diagram in accordance to the Consolidated Standards of Reporting Trials (CONSORT)

**Fig. 2 Fig2:**
[figure not shown]
SPIRIT figure: Schedule of enrolment, interventions, and assessments

### Inclusion and exclusion criteria

Eligible adolescents from the assigned schools will be asked to take part in the study. There are only two criteria for inclusion in the study: Participants must be aged between 11 and 14 years and in the 6th or 7th grade. We chose this age group because epidemiological data show that the end of childhood and the beginning of adolescence represents the period with the highest risk of onset of NSSI [22]. Accordingly, the first rise in incidence rates can be determined around the age of 14 years. Based on the rationale of universal prevention, a program should start before this period, keeping in mind that a universal prevention approach should start before a disorder develops [23]. Likewise, only two exclusion criteria will be applied: lack of informed consent from the adolescents or their relatives, and currently receiving individual psychotherapy because of a mental disorder. If participants report being in individual psychotherapy, to avoid stigmatization, they will still attend the training together with their classmates, and their data will be collected but saved separately. Thus, these participants will still be able to see information about their results, but these results will not be included in the data analysis. This procedure was chosen due to potential confounding effects between individual psychotherapy and the prevention program.

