### Data assessment

Data will be collected and assessed in cooperation with the Institute of Clinical Epidemiology and Biometry, University of Wuerzburg, Germany. The baseline assessment (T0) will take place after randomization and 7 days (± 3 days) before the subsequent start of the treatments. At the end of DUDE or 5 weeks after receiving the minimal intervention (± 7 days), the second measurement (T1) will be conducted. Further assessments will ensue 6 months (± 7 days; T2) and 12 months (± 7 days; T3) after the end of DUDE. After every measurement, the data will be screened for potential suicidality (see the “Emergency procedure” section). At T2, only a selection of the assessment measures will be used (see Fig. 2). We chose this procedure in order to check for iatrogenic effects which could occur immediately after the prevention [24], whereas protective effects, or rather efficacy, in universal prevention is expected later [25]. Additionally, we will evaluate how appealing DUDE is to the adolescents, as this might have an impact on the effectiveness of the program.

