### Harms

In view of the non-invasive universal prevention, the risk for the participants is considered marginal. Comparable studies (i.e., SEYLE study or SOSI) showed no iatrogenic effects such as an increase in suicidality or NSSI. Irrespective of the randomization, participating pupils will benefit from a universal prevention that protects against the development of psychopathology and especially NSSI and suicidality. However, an increase in NSSI and suicidality cannot be completely ruled out. Hence, an emergency procedure has been installed in order to help conspicuous pupils (see the “Emergency procedure” section). Nevertheless, there is no obvious risk for participants. The independent Institute of Clinical Epidemiology and Biometry, University of Wuerzburg, will provide expert advice regarding all aspects of data quality. This means that the data could be checked immediately after data entry for adolescents who are potentially at risk, ensuring that the Department of Child and Adolescent Psychiatry, University Hospital of Wuerzburg, can provide them with the necessary help as quickly as possible. Beyond this, the ethics committee and the Ministry of Education and Cultural Affairs will be informed about adverse events, such as suicidal acts, and the further course of the study will then be coordinated with these entities.

The principal investigators will inform surrounding psychiatric hospitals about the study in advance. Information about where to find help as well as necessary contacts will be publicly available on the study homepage and on the information letters given to the pupils beforehand, ensuring that all participants know how to access emergency contacts. Additionally, we will provide consulting addresses and the study staff will also be available by telephone and mail. If any adolescent feels overwhelmed during the data collection or the training, another emergency protocol is in place to offer help right away. In addition, we will be in close contact with the respective educational psychologists throughout the duration of the study to ensure that psychiatric/psychotherapeutic help can be easily provided if needed.

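### Pupils in individual psychotherapy receive DUDE and are measured, but the plan keeps them out of the data analysis without exempting harms, so no between-arm harm result would cover them

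*Protocol article*

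**What the plan says.** The protocol article, under Inclusion and exclusion criteria, excludes pupils who are "currently receiving individual psychotherapy because of a mental disorder". To avoid stigmatization, however, "they will still attend the training together with their classmates, and their data will be collected but saved separately". The pupils may see their own results, but "these results will not be included in the data analysis". The reason given for the exclusion is that it was chosen "due to potential confounding effects between individual psychotherapy and the prevention program". No analysis is exempted from the rule.

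Two other sections bear on harm. Data assessment explains part of the measurement schedule as chosen "in order to check for iatrogenic effects which could occur immediately after the prevention". Harms concedes that "an increase in NSSI and suicidality cannot be completely ruled out".

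The individual safeguards are these. Data assessment states: "After every measurement, the data will be screened for potential suicidality". Emergency procedure sets out what follows when a pupil reports serious suicidal thoughts on the PSS or voices them during a DUDE unit. Harms provides for adverse events such as suicidal acts to be reported to the ethics committee and the Ministry. None of these provisions is stated to leave out the pupils in psychotherapy.

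**The concern.** The exclusion acts on the data and not on exposure. These pupils sit through the programme with their class and fill in the questionnaires, but their answers do not enter the results. Confounding with psychotherapy is a reason that concerns the efficacy estimate at most. It does not explain why exposed pupils should be absent from a comparison of harm between arms: schools are randomised, so control schools also contain pupils in therapy.

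The Discussion presents the school setting as a way to reach every pupil, so pupils in therapy would also receive DUDE in routine use. The Background links NSSI strongly to comorbid psychopathology. It is therefore reasonable to expect more NSSI in this group, although the protocol does not quantify this. If the rule is followed as written, a rise in NSSI confined to these pupils would not appear in any comparison between arms, although the data to show it would have been collected.

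**Working it through.** **Texts side by side**

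| Question | Where | Answer in the text |
|---|---|---|
| Are these pupils exposed? | Inclusion and exclusion criteria | Yes, they attend with their class |
| Are they measured? | Same | Yes, data collected and stored apart |
| Are they analysed? | Same | No, without exception |
| Is harm a purpose of measurement? | Data assessment | Yes |
| Is harm considered possible? | Harms | Yes, for NSSI and suicidality |
| Are they screened individually? | Data assessment, Emergency procedure, Harms | Not stated to be left out |
| Does the questionnaire trigger cover NSSI? | Emergency procedure | It names suicidal thoughts on the PSS, not NSSI |

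The individual safeguards act on single pupils. They do not compare arms, and the questionnaire trigger works on suicidality. What is missing is a group-level result by arm, and mainly one for NSSI.

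**The plan's own figure.** Sample size gives 160 analysed pupils per school, 20% dropout and 16 schools: 160 / (1 - 0.20) = 200 per school, and 200 x 16 = 3200, of whom 1600 are in DUDE schools. This agrees with the text.

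**Pupils affected.** The protocol gives no share in psychotherapy, so the share p is an assumption:

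| p | DUDE schools, 1600 x p | All schools, 3200 x p |
|---|---|---|
| 2% | 32 | 64 |
| 5% | 80 | 160 |
| 10% | 160 | 320 |

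**What could go unseen.** Suppose, for illustration only, that NSSI rises by 10 percentage points in this group. Extra cases = 1600 x p x 0.10, which is 3.2, 8 or 16 pupils. Spread over all 1600, that is 0.2, 0.5 or 1.0 percentage points.

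**What a stratum could show.** Assume an NSSI risk of 10% in both arms and n pupils in therapy per arm, and ignore clustering and dropout, both of which widen the interval. The half-width of the 95% interval for the risk difference is 1.96 x sqrt(2 x 0.10 x 0.90 / n):
- n = 32: 1.96 x 0.0750 = 14.7 points
- n = 80: 1.96 x 0.0474 = 9.3 points
- n = 160: 1.96 x 0.0335 = 6.6 points

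At n = 80, an assumed risk of 5% gives 1.96 x sqrt(2 x 0.05 x 0.95 / 80) = 6.8 points, and 20% gives 1.96 x sqrt(2 x 0.20 x 0.80 / 80) = 12.4 points. The stratum is descriptive at any of these sizes.

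**Power.** With 2.31% against 0%, ICC 0.015 and 160 pupils per school, the design effect is 1 + 159 x 0.015 = 3.385 and the effective n per group is 1280 / 3.385 = 378.1. An unpooled z-test then has 84.9% power. If 10% are excluded on top of dropout (144 per school), it has 83.7%. The stated 80% can be reached by standard variants: a t reference with 14 degrees of freedom gives 79.4%. The exclusion hardly affects power; the issue is who is covered by the harm results.

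**The case against.** **It is a disclosed and reasoned exclusion.** This is true, and for efficacy it can stand. The reason given does not extend to harm.

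**The pupils are still protected.** A reader might infer that they are unmonitored. The documents do not support that. The suicidality screen follows every measurement, the emergency procedure and adverse-event reporting are not restricted to analysed pupils, and the protocol calls these pupils participants. For suicidality, the gap therefore lies only in the results by arm.

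**The article specifies no harm analysis, and details may be in the statistical analysis plan.** This stands in part. Statistical analysis defines no safety population, and its absence from an article is no fault. The excluding sentence might also have been meant for efficacy alone. But it is a rule without qualification, and a later plan that analysed these pupils would contradict it.

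**The intention-to-treat statement already includes everyone randomised.** Statistical analysis does promise this, but the exclusion rule is the more specific text, and Procedure and randomization places the eligibility check after randomisation of schools. The statement does not clearly bring these pupils back, and the two sections should be reconciled in the same edit.

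**A small stratum proves little.** This is correct, and it limits what the fix can deliver. A small, visible stratum still tells the reader more than an absent one.

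**Conclusion.** The point holds as a limited gap. Pupils in individual psychotherapy are exposed to DUDE and measured, but excluded without qualification from the analysis, so no between-arm result on harm would include them. The gap matters chiefly for NSSI. It is worth fixing because the data are collected anyway; it does not undermine the primary analysis.

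The size is unknown. The range of 32 to 160 of 1600 DUDE pupils rests wholly on an assumed share of 2% to 10%, and that the group is at higher risk is an inference from its treatment for a mental disorder.

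Two stronger readings are not supported. A reader might assume a three- to fivefold NSSI risk and conclude that a large part of the programme's harm would be missed. Such a figure would describe NSSI already present in pupils under treatment and would say nothing about NSSI caused by DUDE. A reader might also infer that the trial will declare DUDE free of iatrogenic effects in these pupils. No section says so, and Harms is itself cautious.

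**What to change.** - In Inclusion and exclusion criteria, limit the exclusion of pupils in individual psychotherapy to the efficacy analyses.
- In Statistical analysis, add that NSSI (DSHI-9) and suicidality (PSS) will also be summarised by randomised arm, at each time point where they are measured, for all consenting pupils in DUDE and control schools. Attendance should not be a condition, because attendance at DUDE has no counterpart in control schools.
- Show pupils who report psychotherapy at baseline as a separate descriptive stratum in each arm. Baseline follows randomisation, so the summary of all consenting pupils should come first: it does not depend on how therapy status was reported.
- Let any statement about iatrogenic effects give the size of this stratum and say that it is too small to exclude harm.
- Reconcile the exclusion with the intention-to-treat statement.

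The cost is a few sentences, one extra table, and linkage of the separately stored data to arm. As a change to a stated exclusion, it would probably also need an amendment to the ethics committee and the Ministry under Ethical issues and dissemination. No new data are collected, and the sample size and emergency procedure are unchanged. The downside is a small stratum that can only be described.
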